### Study Design

This study is a parallel-group, randomized controlled superiority trial with two groups (ie, intervention and control) having an allocation ratio of 1:1. The trial was registered at ClinicalTrials.gov (NCT04216446) on January 2, 2020. The intervention to be tested is an mHealth program that was developed locally to collect dietary, supplement use, and physical activity information from pregnant women and to provide personalized counseling tailored to the screening information. The control group will receive standard counseling with similar content, but the content will not be personalized and will be delivered through face-to-face sessions.

### Study Setting

The study is taking place at the Aga Khan University Hospital (AKUH) in Karachi, Pakistan. AKUH is a private, not-for-profit, tertiary care hospital, recognized for its trained health care professionals who specialize in providing high-quality compassionate care and for a full range of specialty services [42]. It is also certified by the Joint Commission International Accreditation. The study participants were recruited on a daily basis from the antenatal clinics that are run by trained obstetricians. Most obstetricians, on average, see 25 to 30 pregnant women every day in the clinic.

### Enrollment Criteria

Pregnant women 18 years or older and in their first trimester are eligible to participate if they possess a personal smartphone with internet connection and agree to remain in the study until 1 year following the birth of their baby. Pregnant women on dietary control secondary to the diagnosis of diabetes mellitus; taking medications, such as antiplatelet aggregators, hypoglycemic drugs, or antihypertensive drugs; who have autoimmune, liver, or kidney disease; or who are unable to read and write due to a language barrier will be excluded from the study.

### Sampling Strategy and Randomization

Participants were identified using a purposive sampling strategy and were randomly assigned to the study groups using simple block randomization (block size of 6). The Clinical Trials Unit at AKUH facilitated the computer-generated randomization and provided opaque, sealed envelopes to the research team to ensure concealment of the assignment (Figure 1).

**Figure 1 figure1:**
[figure not shown]
CONSORT diagram of the study. AKUH: Aga Khan University Hospital; mHealth: mobile health.

### Recruitment

At the antenatal clinics, participants were approached to assess their eligibility and to obtain written informed consent. The data collector explained, in detail, the study’s aims and procedures involved in order to facilitate women’s participation and ensure compliance in the study. A signed copy of the consent form was provided to the participants. Enrolled participants were randomized to one of the two groups (Figure 1).

### Web-Based mHealth Program: PurUmeed Aaghaz

The web-based mHealth program, called *PurUmeed Aaghaz* (a hopeful beginning), was designed and developed locally with the assistance of the Digital Health Resource Center (DHRC) of the Aga Khan Development Network. It is an online, device-dependent app designed to function on Android and iPhone operating systems. It was developed based on the scientific evidence of recommended dietary, supplement use, and physical activity guidelines during pregnancy. Moreover, the coaching platform takes into consideration the theory of planned behavior [43], the theory of self-efficacy [44], the Fogg behavior model [45], and the transtheoretical model for behavior change [46]. Furthermore, the preference, availability, and consumption of locally available items from all the major food groups; supplement use (ie, folic acid, iron, calcium, and vitamin D); and physical activity were taken into account during the development of the app. Based on the participants’ data, the app will generate tailored and personalized counseling messages and recommendations for the pregnant women regarding diet, supplement use, and physical activity. This app will be available to the participants who are randomized to the intervention group as a free subscription, starting from enrollment during their first trimester and for the entire duration of their pregnancy (Figure 2).

**Figure 2 figure2:**
[figure not shown]
Screenshots of the *PurUmeed Aaghaz* app.

### Features of the mHealth Program

The mHealth program has three main features, as discussed in the following three sections.

#### Personalized Recommendations and Dietary Risk Scores

Submission of completed questionnaires by the participants in the first trimester will generate recommendations based on an algorithm. This algorithm will compare participants’ information with the recommended dietary [47], supplement use [48-50], and physical activity guidelines [19] for pregnant women as described in the Counseling for Diet, Supplement Use, and Physical Activity section below. In addition, individualized dietary risk scores for food quantity and diversity in diet will also be generated.

#### Push Messages

Content from the individual coaching sessions will be delivered three times a week in the form of short push messages containing tips and recommendations for diet, supplement use, and physical activity. These messages will be short, simple, and easy to comprehend. Women will be alerted to these messages through notifications on their phones, and these will be available in the app under the “advice” option.

#### Food Record Diary

A built-in food record diary will be available to document information about the food items consumed in a day for breakfast, lunch, dinner, and snacks, along with their portions. Women will be asked to complete the food record diary in their smartphones for a week before their next follow-up, so as to reduce the chance of recall bias. On the follow-up day, the diary will be synced with the data collection tool. Any missing information will be added during the interview.

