**Methods:**

A randomized controlled trial was initiated at the Aga Khan University Hospital in Karachi, Pakistan, in January 2020. We aim to recruit 300 pregnant women in their first trimester who have smartphones, do not have comorbidities, and are not taking medications. The intervention group will be trained to use an mHealth app called *PurUmeed Aaghaz*. Through this app, the subjects will report information about their diet, supplement use, and physical activity and will receive personalized advice and three push messages as weekly reminders. The research assistant will obtain similar information from the control group via a paperless questionnaire; this group will receive standard face-to-face counseling regarding diet, supplement use, and physical activity. Data will be collected at enrollment and during four follow-up sessions scheduled 6 weeks apart. Primary study outcomes include improvements in diet (ie, change in mean dietary risk score from baseline to each follow-up), supplement use (ie, changes in mean supplement use score and biochemical levels of folic acid, iron, calcium, and vitamin D on a study subset), and mean duration of reported physical activity (minutes). Secondary study outcomes relate to maternal health (ie, gestational diabetes mellitus, gestational hypertension, pre-eclampsia, and gestational weight gain), newborn health (ie, birth weight and length and gestational age at delivery), and infant health (ie, BMI and blood pressure at 1 year of age). Compliance will be determined by the proportion of participants who complete the 6-month coaching program. Usability will be assessed based on features related to design, interface, content, coaching, perception, and personal benefit.

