### Control Group

Women randomized to the control group will provide their dietary, supplement use, and physical activity information on a paperless questionnaire administered by the research assistant. Face-to-face counseling will follow, using the bilingual educational brochure from the AKUH on diet during pregnancy and ACOG guidelines for physical activity [19]. A copy of the educational brochure and a paper-based food record diary to be filled in a week prior to their next follow-up will also be provided to women in the comparison group.

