### Data Collection Tools

#### Screening Questionnaire

A comprehensive questionnaire has been developed to collect data from the participants on sociodemographic characteristics, general food information, anthropometric and blood pressure measurements, biochemical assessments, obstetrics history and supplement use, dietary consumption for the past 7 days recorded as quantity and quality of each food group, and physical activity history for the past 7 days. In addition, intake of savory and fast food, water, tea, coffee, carbonated beverages, and substances such as smoked and smokeless tobacco will be recorded. The questionnaire has been developed after consulting experts and reviewing various dietary assessment tools and programs, such as the 24-hour dietary recall [55], food frequency questionnaires [55], and the Smarter Pregnancy program [56]. The questionnaire has been pretested on 5% of the sample and has been further improved.

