### Expected Primary Outcomes

#### Dietary Intake: Quantity and Quality

Change in dietary intake between baseline and four subsequent follow-up visits 6 weeks apart will be assessed through a questionnaire. Based on consumption recorded in the food diary, data will be collected on the frequency and amount of all kinds of food consumed at each meal, including fruits and vegetables, red meat, white meat, legumes, nuts, eggs, dairy products, added table salt, and drinks (eg, carbonated drinks, fresh juices, and prepared juices). Averages will be calculated to determine the daily intake. Food sizes and amounts will be explained with the help of model utensils (ie, plate, bowl, and glass).

Dietary risk scores, ranging from 0 to 18, will be calculated based on the consumption of food items from six main food groups. Based on portions and diet quality, the score for each food group will be 0, 1.5, or 3 (Table 1) [58]. The total score will be the sum of individual food group scores. The higher the aggregate score, the poorer the dietary quantity and quality, and vice versa. Hence, a score of 18 indicates a highly inadequate dietary intake, a score of 9 indicates a nearly adequate dietary intake, and a score of 0 indicates an adequate diet [58].

**Table 1 table1:** Dietary risk score for six food groups.

Food group and characteristics^a^		Dietary risk score		
		0	1.5	3

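### Dietary change from baseline compares a recall-based score with diary-fed follow-up scores, so within-arm improvement and any percent-of-baseline target may partly reflect the change of data source

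*Protocol article*

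**What the plan says.** The Abstract (Methods) defines the primary diet outcome as "change in mean dietary risk score from baseline to each follow-up". The section Dietary Intake: Quantity and Quality adds: "Change in dietary intake between baseline and four subsequent follow-up visits 6 weeks apart will be assessed through a questionnaire". It then says that the intake data are based on what the food diary records.

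The data behind the score differ by visit:

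- **Baseline, both arms.** The Screening Questionnaire section describes "dietary consumption for the past 7 days recorded as quantity and quality of each food group", which is retrospective.
- **Follow-up, intervention arm.** The Food Record Diary section (under Features of the mHealth Program) says: "Women will be asked to complete the food record diary in their smartphones for a week before their next follow-up". The stated purpose is "so as to reduce the chance of recall bias". It continues: "On the follow-up day, the diary will be synced with the data collection tool". For gaps: "Any missing information will be added during the interview".
- **Follow-up, control arm.** The Control Group section provides "a paper-based food record diary to be filled in a week prior to their next follow-up".

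The Study Hypothesis expects diet to improve by 30% over the study period. The Sample Size Calculation expresses this as a 30% improvement in the intervention group starting from 20%. The Primary Objective sets the same 30% against face-to-face counseling.

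**The concern.** A change from baseline can be read as a change in behaviour only if both ends are measured in a comparable way. Here one end rests on memory alone and the other on a record kept as the week goes by. The plan uses the diary to limit recall error, so it has reason to expect the two sources to differ to some extent, yet the outcome subtracts one from the other.

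Three things are at stake:

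- any statement that diet improved, or did not, within an arm since enrolment;
- any target expressed as a percentage of the baseline value;
- the precision of raw change scores, if the differently measured baseline correlates less well with follow-up.

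The issue does not depend on app versus paper. It would remain if both arms used the same diary.

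**Working it through.** **1. Data source by visit.** The screening questionnaire covers the 7 days before enrolment. Each diary covers the 7 days before the next follow-up, in both arms. A diary therefore feeds 0 of 1 baseline visits and, as planned, 4 of 4 follow-up visits. No baseline or run-in diary and no calibration of the two sources is described.

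**2. The plan's own figure.** Inputs from the Sample Size Calculation: 20% to 50%, α = .05 (taken as two-sided), power 80%, 1:1.

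- Uncorrected: n' = [1.96 × √(2 × 0.35 × 0.65) + 0.842 × √(0.20 × 0.80 + 0.50 × 0.50)]² / 0.30² = 38.5, that is 39.
- With continuity correction: n = (n'/4) × [1 + √(1 + 4/(n' × 0.30))]² = 44.9, that is 45 per group, as stated.

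The figure is not disputed. It shows that the 30% was powered as 30 percentage points in a proportion.

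**3. A shift shared by both arms.** The documents give no size, so assume that moving from recall to diary changes the share scored adequate by s points, equally in both arms. Let the true change be +30 points in the intervention arm and 0 in controls, from a recall baseline of 20%.

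- Apparent change, intervention: (50 + s) − 20 = 30 + s
- Apparent change, control: (20 + s) − 20 = s
- Between-arm difference: (50 + s) − (20 + s) = 30

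| s (points) | Intervention change | Control change | Between-arm difference | n per group (method of step 2) |
|---|---|---|---|---|
| −10 | 20 | −10 | 30 | 38 |
| −5 | 25 | −5 | 30 | 42 |
| 0 | 30 | 0 | 30 | 45 |
| +5 | 35 | +5 | 30 | 48 |
| +10 | 40 | +10 | 30 | 49 |

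The within-arm figures absorb the whole shift. The between-arm contrast does not, and the required number hardly moves.

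**4. The same question on the 0 to 18 score.** Mean baseline scores are not given, so assume 6, 9 or 12. A 30% improvement is then 1.8, 2.7 or 3.6 points. Scores move in steps of 1.5 per food group.

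- If every woman moved one level in one food group (1.5 points), the shift would be 1.5/1.8 = 83%, 1.5/2.7 = 56% or 1.5/3.6 = 42% of the target.
- If half of them did (0.75 points), it would be 42%, 28% or 21%.

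A percent-of-baseline target also inherits the scale of the recall score. With a recall mean of 9 and a shift of −0.75, the diary-equivalent baseline is 8.25, and 30% of it is 2.475 rather than 2.7 points.

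**5. Precision.** Assume equal variance σ² at baseline and follow-up, and correlation ρ between them.

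- Follow-up score alone: σ²
- Change score: 2σ²(1 − ρ), which exceeds σ² whenever ρ < 0.5
- Follow-up adjusted for baseline: σ²(1 − ρ²)

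At an assumed ρ of 0.3, 0.5 and 0.7, the change score has variance 1.40, 1.00 and 0.60 times σ². The adjusted analysis has 0.91, 0.75 and 0.51 times σ². Adjustment is never worse than subtraction here, and its advantage grows as ρ falls.

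**The case against.** The strongest reply is that the plan already makes the right comparison. The Primary Objective compares with face-to-face counseling, the design is a parallel-group superiority trial, and the Statistical Analysis section plans group comparisons plus a mixed model for the fraction scoring adequately at the follow-up times. No within-arm test is planned, and a shared shift drops out of a difference between arms. This largely stands, and step 3 bears it out. A reader might infer that the primary randomised comparison is biased; the documents do not support that. Cancellation need not be exact, because the score has cut-offs and the same reporting shift can move different numbers of women across them once the arms' intakes differ. That is a refinement, not grounds for calling the comparison invalid.

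A second reply is that the instrument has not really been replaced. A questionnaire is named for all visits, the recall and diary windows are both 7 days, only one scoring table is given, and the interview fills diary gaps. This also stands in part: follow-up is a diary-aided questionnaire, not a pure diary. But what feeds the questionnaire still changes, and it changes between baseline and week 6.

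A third reply is that the size is speculative. It is. A reader might infer that a step between baseline and week 6 must appear, or that it would favour improvement. The text shows neither, and the 21% to 83% range rests on assumed means and assumed shifts. It also does not bear on the powered contrast, which is a difference in proportions.

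The biochemical subset cannot settle the matter. It covers 30 women per group at baseline and study end only, and its markers also respond to the counseled supplements. Whether app and paper diaries differ is a separate question and lends this point no weight.

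**Conclusion.** The point holds in a limited form. Baseline diet rests on 7-day recall and every follow-up score is fed by a 7-day diary with interview gap-filling, in both arms. Change from baseline, and the 30% improvement worded from baseline, may therefore mix data source with behaviour.

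The effect falls on within-arm statements, percent-of-baseline targets and the precision of raw change scores. Under an assumed common shift of −10 to +10 points, within-arm change is off by the full shift while the between-arm difference stays at 30 points and the required number stays between 38 and 49 per group. This rests on the shift being additive and roughly equal in the two arms; its actual size and direction are unknown. It is worth correcting because the article itself fixes both the data sources and the outcome definition, and the correction is cheap.

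**What to change.** Recruitment is complete, so a baseline diary can no longer be collected. The change is to the wording of the outcome and analysis:

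- Define the diet effect as the between-arm difference in diary-based score, or in the fraction scoring adequately, at weeks 6, 12, 18 and 24.
- Keep the recall-based baseline score as a covariate instead of subtracting it. Discarding it is unnecessary and would lose precision.
- Judge the 30% target on that between-arm contrast.
- Limit within-arm trends to weeks 6 to 24, and label any baseline-to-week-6 change as including a change of data source, not as improvement.

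No new data are needed. The downside is that improvement within an arm since enrolment can no longer be claimed for diet.

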### Counseling for Diet, Supplement Use, and Physical Activity

#### Diet

Women randomized to the intervention group will receive dietary advice based on the World Health Organization (WHO) guidelines for healthy eating during pregnancy and breastfeeding [47]. We have also consulted guidelines by the WHO for healthy diet [51], the ACOG for nutrition during pregnancy [52], and the Food and Agriculture Organization of the United Nations [53] for the development of content for the push messages. In these messages, consumption of food from six main food groups will be encouraged as follows: bread, cereals, rice, and potato group (6-11 portions per day); vegetable group (at least 3 portions per day); fruit group (at least 2 portions per day); milk and dairy products group (3 portions per day); fish, poultry, meat, and beans group (2 portions per day); and butter, margarine, and oil group (less than 30% of total calories, preferably as unsaturated fats) [51]. In addition, women will be advised to consume three meals and two snacks per day to avoid prolonged periods of fasting and to consume monounsaturated fats, adequate protein, fiber-rich carbohydrates, and at least two servings of omega-3–rich fish per week. Consumption of vitamin A will be encouraged from plant sources as beta carotene. Further, advice will be given to limit intake of carbohydrates with a high glycemic index (eg, fruit juices and sodas).

#### Supplement Use

WHO guidelines for micronutrient supplements during pregnancy will be used to counsel women. These will include daily oral supplements of folic acid (0.4 mg) [48], iron (30-60 mg) [49], calcium (1500-2000 mg) [49], and vitamin D (200 IU) [50].

#### Physical Activity

Based on ACOG guidelines [19], women will be advised to engage in moderate-intensity aerobic physical activity for at least 150 minutes over the week or 30 minutes on most days of the week. Moreover, they will be encouraged to limit prolonged periods of being sedentary [54].

### Control Group

Women randomized to the control group will provide their dietary, supplement use, and physical activity information on a paperless questionnaire administered by the research assistant. Face-to-face counseling will follow, using the bilingual educational brochure from the AKUH on diet during pregnancy and ACOG guidelines for physical activity [19]. A copy of the educational brochure and a paper-based food record diary to be filled in a week prior to their next follow-up will also be provided to women in the comparison group.

### Follow-Up

Follow-ups will be done four times, every 6 weeks: 6, 12, 18, and 24 weeks from the time of enrollment in the first trimester to monitor improvement, if any. For the intervention group, results of each follow-up and their comparison with the earlier one will be displayed on each participant’s personal page of the app. A summary of the individual results will be able to be viewed at any moment by the participant and handed over or shared with their obstetrician by email for further assessment and care. The control group will receive face-to-face counseling at each follow-up.

### Data Collection Tools

#### Screening Questionnaire

A comprehensive questionnaire has been developed to collect data from the participants on sociodemographic characteristics, general food information, anthropometric and blood pressure measurements, biochemical assessments, obstetrics history and supplement use, dietary consumption for the past 7 days recorded as quantity and quality of each food group, and physical activity history for the past 7 days. In addition, intake of savory and fast food, water, tea, coffee, carbonated beverages, and substances such as smoked and smokeless tobacco will be recorded. The questionnaire has been developed after consulting experts and reviewing various dietary assessment tools and programs, such as the 24-hour dietary recall [55], food frequency questionnaires [55], and the Smarter Pregnancy program [56]. The questionnaire has been pretested on 5% of the sample and has been further improved.

#### Food Record Diary

Information about the frequency and portions of food consumed from different food groups over 7 days before the participants’ next follow-up will be collected in the food record diary. The intervention group will report this information in the *PurUmeed Aaghaz* app, while the control group will be required to record this information in a paper-based diary.

